#### *The FCC care provision*

The perception of multiprofessional staff members on parent support they have given that day is measured with DigiFCC web-questions. The question will reflect the staff's point of view on the support provided for parents in following dimensions: 1) active listening, 2) parent participation in infant care, 3) individualized parent education, 4) parent participation in decision-making, 5) the parent trust staff in infant care, 6) the staff feel the parents trust them in infant care, 7) participation in medical round/medical care decision making, 8) information sharing, and 9) emotional support. Staff members answer the questions through a website which is always open at the research computer in the unit. The computer is connected to the Internet. Every staff member (regardless of qualifications) working in the participating units is asked to answer a daily question through a website after their each work shift for a 3-month period. There are 9 questions which are randomized in 3-question blocks. Answers are numbers from 1 to 5 or 0 if the staff member hasn't been working with the parents on that shift or didn't participate in the medical round. In addition to the number, they had space to write free text. The staff members are provided with the instructions of Web-questions.

Regarding the same 3-month period, the researcher/administrator collects the number of nursing staff work shifts in the unit to calculate the response rate. The research will create a questionnaire for each unit through the Master account website. The responsible researcher will have an access to Research account to collect the answers.

#### Methods to assess the impact of the intervention on parents

##### *Infant-parent background questionnaire*

A questionnaire is used to collect background information of infants/parents (Appendix 5)

##### *Parents' depressive symptoms*

The depressive symptoms of parents are measured with Edinburgh Postnatal Depression Scale (Appendix 6) (EPDS). The 10-question EPDS is a valid method to measure depressive symptoms both in mothers and in fathers. The 10-question scale includes symptoms such as insomnia, mood, tearfulness, and the thoughts of self-harm. The scale asks how the parent has felt during the previous week. The parents rate each question on a scale from 0 to 3. The maximum score on the EPDS would be 30. Parents are asked to fill in the EPDS questionnaire from two to one week before discharge. The EPDS is easy to administer and has high sensitivity as a screening tool.

##### *Parent's anxiety symptoms*

The anxiety symptoms of the parents are assessed with State and Trait Anxiety Inventory (STAI) (Appendix 7). State anxiety is an emotional reaction that varies from one situation to another, whereas the trait anxiety is a personality characteristic. The STAI measurement provides separate scores for both types of anxiety. There are 20 questions about state anxiety that are rated with 4-point scale (1=not at all,

### *Research protocol– [name]*

4=very much) and 20 questions about trait anxiety that are also rated with 4-point scale (1=almost never, 4=almost always). The recommended cut-off for the postnatal anxiety measured with STAI-S is 34/80.

The research assistant will calculate the parent's scores of EPDS and STAI-S when the questionnaires are returned. She informs the responsible researcher of the unit if the total score of the EPDS is >12 or if the parent has suicidal thoughts and if the total score of STAI-S is >33. The local research group will then decide who will contact the parent and refer her to appropriate health care services if needed.

### *Parenting self-efficacy scale*

Parenting self-efficacy is measured Perceived Maternal Parenting Self-Efficacy (PMP S-E) instrument (Appendix 8). The PMP S-E instrument consists of 20 items (scoring ranges 20–80) with four subscales: 1) care taking procedures, 2) evoking behaviors, 3) reading behaviors or signaling, and 4) situational beliefs. The items are rated with a four point Likert scale ranging from 'strongly disagree' (score 1) to 'strongly agree' (score 4). A low score on this scale indicates a low maternal self-efficacy. The PMP S-E tool is a psychometrically robust, reliable and valid measure of parenting self-efficacy in mothers of relatively healthy hospitalized preterm neonates.

### *Parent's readiness for discharge*

The readiness for the discharge is measured with the Readiness for Hospital Discharge Scale (RHDS) (Appendix 9). The questionnaire includes 23 items. Four attributes of readiness for discharge are measured within the subscales: Personal Status (7 items), Knowledge (7 items), Coping Ability (4 items), and Expected Support (5 items). Answers are on a 10-point scale from 0 to 10 (e.g., not at all, totally). The RHDS has shown to be a reliable and valid measure of patients' perception of readiness for discharge.

### *Parent's perceived FCC*

The parent participation and the support parents feel they receive from the staff is measured using questionnaire modified from DigFCC SMS questions (Appendix 10). The questionnaire includes 9 questions covering following aspects of staff support 1) active listening, 2) parent participation in infant care, 3) individualized parent education, 4) parent participation in decision-making, 5) the parent trust staff in infant care, 6) the parent feel the staff trust them in infant care, 7) participation in medical round/medical care decision making, 8) received information, and 9) emotional support. The parents are asked to rate separately their experience of the each hospital unit they have stayed during the hospitalization of their baby. They are asked to answer the question with the Likert scale from 1 to 7 (1=not at all–7=very much; 0= if they did not visit the unit). This questionnaire can be handed out solely for the families that have stayed in a unit at least three days but their infant is transferred to another unit.

### Data management

We will utilize REDcap (Research Electronic Data capture) for the data transfers from Estonia to Finland and for the data storage. REDcap is an electronic tool for data collection that is provided from the server facilities owned and operated by the University of Turku IT Services, which also means all data collected

to the system is stored and kept at the University of Turku. When the data is stored to the online file storage of Turku University it is automatically copied to three independent servers that also function as data backup systems. The data is entered to the REDcap system by the local research assistant/ research nurse.

Data security description:

- Centralized administration by separate administration accounts and compartmentalized user privileges
- Use of current and reliable hardware, and software which is updated continuously
- Centralized identity management (IDM)
- Locally administered industry-standard network infrastructure and services
- Common server platforms with minimal tailoring
- Continuous monitoring of network traffic patterns and service statistics
- Widely deployed security software and other monitoring tools

The PI controls the access to the data. The co-researchers can approach the PI to request access to the data. The PI will apply to the University of Turku IT Services to provide the access to the online storage. If a co-researcher is not working at the University of Turku, the PI can ask the IT services to give that person a visitor status and, thereby, an access to the online file storage. All new users are identified using government-issued identification documents or by citizens' identification and payment service. The allowance to access the data is issued only for the active research period and ends when the research is completed. The IP will keep a record of those who have active access to the data.

All the data will be handled anonymously. The participants will get an ID code that is used when data is stored and analyzed. The recruitment log of the parents and staff members are used to undo the ID codes and, therefore, they are kept separately from the data files. The analytic softwares (Google Analytics, Hotjar and Vimeo) also track anonymously participants' behavior on the e-learning module's website. The personal details (password, email, etc) are not recorded and the IP addresses are anonymized by cutting out the last few digits, so only the rough geographical area of access to the e-learning module is identified. The logs and all the data will be destroyed five years after the last publication from the data.

The intervention

The Close Collaboration with Parents intervention will be carried out in the four NICUs in Estonia. The delivery of the intervention follows a structure that has been developed and fine-tuned between 2009 and 2020 when it was implemented in 14 NICUs. First, experienced nurses or doctors from the units will undergo a three-week training to become "unit mentors," and then these unit mentors will train other members of staff. The training of the units is strongly based on experiential learning utilizing bedside practices, reflection of the practices, and application of this knowledge in everyday clinical situations. Theoretical teaching, which precedes clinical bedside mentoring, will occur through a new e-learning tool. Each staff member will spend about four working days training alongside his or her routine work. The unit mentors will function as facilitators for all the staff, and they have dedicated time for this. The content of the bedside practices is guided by a manual. To support the delivery of this phase, the training

team will provide frequent remote supervision for the unit mentors and leadership. The units have committed to allocate the resources for the implementation of the intervention. The applicant will have the main responsibility for the delivery of the training. The aim is to train about 75% of the staff members in the units during the 18-month period.

### **Translation process**

The following study material needs to be translated by official translator/linguistic to Estonian and Russian and by an independent other official translator/linguistic back to English: the Collaborative Competence -questionnaire, the Reflective Thinking Measure, and Perceived Maternal Parenting Self-Efficacy Instrument, Readiness for Hospital Discharge Scale. After the back-translation, a cognitive debriefing session will be organized to check the validity of the translation. Other methods already exist in Estonian and Russian. Also the following study material can be translated by a translator who is fluent in English and target language: information leaflets about study, informed consent forms and the instructions for the participants.

### **Ethical considerations**

An ethical approval will be asked for the study protocol according to the regulations of each participating hospital. The study protocol needs to get a favourable statement from the Ethics Committee in each country before the data collection can begin. Written informed consent will be obtained from each staff member and parent before study participation. The analytic software (Google Analytics, Hotjar and Vimeo) will be activated only after the consent has been obtained from a participant. The application for ethics should include an opportunity to complete the information received from the parents (infant and family characteristics questionnaire) using patient medical records.

### **Conducting the Research: The tasks of the Local Research Assistant/ Research Nurse**

#### **1. Initiation of the study (1-2 days)**

- To inform the unit and set up the study
- to make information leaflets available, computer setup, reinforcement

#### **2. Recruitment by a research assistant or staff members (nurses/head nurses/doctors) responsible 1-1½ hours per every weekday**

- to check daily the patients who are going to be discharged within a week
- to approach the families with the written study information
- to approach the families for the written consent the following day
- to collect the information of the non-recruited patients (see Appendix A\_Log for Study)
- to handout the questionnaires to the recruited families and collect the filled in questionnaires before the baby is discharged. Resources are needed for recruitment for a 3-month period before the intervention and 3-month period after the intervention. The work time is estimated to be from ½ to 1 hour on each week day (preferably also on weekends).

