## Materials and Methods

### Design

A quasi-experimental before and after intervention design is used to test the effect of the intervention, where the impact mechanisms are treated as mediators of the change.

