### Sample

The subjects are employees of five neonatal units of three Estonian hospitals participating in the Close Collaboration with Parents intervention (hereinafter: staff) and newborns cared for in the units and their parents (hereinafter: families). Three of the units are at Tallinn: West-Tallinn Maternity Hospital (NICU and neonatal unit), the Department of Anesthesiology and Intensive Care (PICU/level IIIB) and the Department of Neonatal and Infant Medicine (NICU/level II) at the Children’s Hospital. The Department of Anesthesiology and Intensive Care is an open-bay intensive care unit, while the Department of Neonatal and Infant Medicine is a single-family-room unit. Another two units are located in Tartu University Hospital: the Department of Neonatal and Pediatric Intensive Care (PNICU, level IIIC) and a stepdown unit (level II). PNICU is an open-bay unit while the stepdown unit has two open-bay intensive care rooms (mothers have their bed in another room of the ward) and 8 single-family rooms.

The inclusion criteria for the families are: 1) families whose newborns have been hospitalized during the first 28 days of infant life, 2) expected length of stay of the newborn is at least three days, 3) discharge is planned to happen within a week, and 4) at least one parent has agreed to participate in the study. The staff working in the units during the entire study period is eligible for the study.

Families are recruited during a four-month period before and after the intervention, with the aim to recruit at least 50 families per participating hospital in both periods. Some newborns may be treated in a different hospital or in different units of the same hospital. In the case of a transfer, the family is asked to fill in only the Family Center questionnaire (Appendix 10) if the newborn has been in that unit for more than 72 hours.

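### Unit staff who are trained and rated may also recruit the families and collect the parents' forms, so a bias that differs between periods cannot be separated from the intervention effect

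*Protocol*

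**What the plan says.** Conducting the Research, item 2, is headed "Recruitment by a research assistant or staff members (nurses/head nurses/doctors) responsible". The tasks under it are a daily check for patients due to go home within a week, "to approach the families with the written study information", seeking consent the next day, recording the non-recruited, and "to handout the questionnaires to the recruited families and collect the filled in questionnaires before the baby is discharged". A member of the unit's staff may therefore do all of these in place of a research assistant.

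Sample defines staff as the employees of the participating units. The intervention description at the end of Data management says of them: "The aim is to train about 75% of the staff members in the units during the 18-month period". Under Parent's perceived FCC, "the support parents feel they receive from the staff is measured using questionnaire modified from DigFCC SMS questions"; its nine items include listening, trust and emotional support. Design states: "A quasi-experimental before and after intervention design is used to test the effect of the intervention".

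The Protocol has some related safeguards. A log of all infants discharged home is kept to assess drop-out and bias; its listed contents are gestational age, birth weight, diagnosis, feeding type and length of stay. Data are stored and analysed under ID codes. On the mood questionnaires, Parent's anxiety symptoms says: "The research assistant will calculate the parent's scores of EPDS and STAI-S when the questionnaires are returned". High scores or suicidal thoughts are then passed to the unit's responsible researcher.

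**The concern.** The people whose support is being rated may approach the raters and take back the completed forms while the infant is still in their care. Two biases can follow. Families who get on badly with staff may be approached less often or less persuasively. Parents who hand a form to a carer may also answer less candidly.

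With no concurrent control, the effect estimate is the difference between periods. Bias of equal size before and after would largely drop out of it. Bias that changes would not, and there is a plausible reason for change: staff know which period they are in, and by the second one most should have been through the programme. Nothing requires the same type of recruiter in both periods.

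The outcomes are not equally exposed. Courtesy scoring bears mainly on the family-centered care form, the one on which parents rate the staff. For EPDS and STAI the issue is who gets recruited and whether parents disclose distress on a form that the treating team may see.

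**Working it through.** The Protocol gives no alpha, SD or power for these comparisons, so there is no figure to reproduce. What follows is an illustration, not an estimate of the actual bias.

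**Inputs**
- Families per period: 3 hospitals × 50 = 150. Both numbers are from Sample, where 50 is a minimum target.
- Assumed: two-sided 5% test, normally distributed score with SD 1, independent families, no true effect, bias in the post period only.

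**Standard error of the difference**

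SE = √(2/150) = 0.115 SD.

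**Selective approach.** Suppose the lowest fraction q of families, as staff judge them, is missing after training. If the staff's judgement correlates ρ with the outcome, the post mean rises by

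shift = ρ × φ(z_q)/(1 − q),

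where φ is the standard normal density and z_q the q-quantile.

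- q = 0.05: φ = 0.1031, and 0.1031/0.95 = 0.109 SD at ρ = 1.
- q = 0.10: φ = 0.1755, and 0.1755/0.90 = 0.195 SD at ρ = 1.

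The chance of a significant result is Φ(shift/SE − 1.96) + Φ(−shift/SE − 1.96).

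| ρ (assumed) | q | Shift (SD) | Shift/SE | False-positive rate |
|---|---|---|---|---|
| 0.3 | 5% | 0.033 | 0.28 | 5.9% |
| 0.3 | 10% | 0.058 | 0.51 | 8.0% |
| 0.5 | 5% | 0.054 | 0.47 | 7.6% |
| 0.5 | 10% | 0.097 | 0.84 | 13.5% |
| 1.0 | 5% | 0.109 | 0.94 | 16% |
| 1.0 | 10% | 0.195 | 1.69 | 39% |

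The ρ = 1 rows are an upper bound. Recruitment comes before the forms are completed, so staff cannot see the score.

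**Courtesy scoring.** A shift of 0.1 SD after training only gives 0.1/0.115 = 0.87 standard errors and a rate of about 14%. A shift of 0.2 SD gives 1.73 standard errors and about 41%. The Protocol has no source for either size.

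**Do the safeguards cover this?**
- The log supplies a denominator and can show imbalance in infant and stay variables. None of its listed variables describes parents' mood or their rapport with staff, and it has no bearing on courtesy scoring. The recruiter also collects the information on non-recruited patients.
- ID codes govern storage and analysis, not who sees a form when it is handed back.
- Scoring by the research assistant begins once the forms are returned. The text does not say that they reach the assistant without passing through carers.

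**The case against.** Staff recruitment is only one of two permitted routes, and the list stands under the tasks of the local research assistant or research nurse. Nothing shows that staff will be the main recruiters or that the recruiter will change between periods. This stands, and it makes the point one of exposure rather than of demonstrated bias. It does not remove the permission.

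A reader might infer that staff are free to pick favourable families. The text does not say so. It describes a daily check of patients nearing discharge, an approach to the families, and a log with a denominator, which reads more like approaching everyone eligible. What remains is that no sentence requires every eligible family to be approached. Appendix A is not shown and may already record reasons.

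A reader might also infer that the bias must flatter the intervention. That is likely but not certain: training meant to build trust could make parents more open about distress, which would work the other way.

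Finally, return arrangements could sit in parent instructions that are not shown, and a sensitivity analysis by recruiter belongs in a SAP. The second point is accepted, and no such analysis is asked for here. On the first, the Protocol itself fixes who collects the forms and when, and an analysis cannot recover families who were not approached or measure courtesy afterwards.

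**Conclusion.** The concern holds in limited form. The Protocol permits trained and rated staff to recruit and to collect the forms in an uncontrolled before-after study, and its safeguards do not reach selection on parents' mood or rapport, or courtesy scoring. A difference between periods in either would be read as an intervention effect.

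The size is unknown. Under the stated assumptions, the nominal 5% error rate becomes about 6% to 8% with weakly informed selection after training, up to 16% to 39% with perfect selection, and about 14% to 41% with a courtesy shift of 0.1 to 0.2 SD. All of these assume that the bias is absent before training; similar bias in both periods would shrink them.

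The documents do not support saying that the results will be inflated, or that every parent outcome is affected by courtesy scoring. The rule leaves an avoidable weakness, greatest for the staff-support ratings, that is cheap to close.

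**What to change.** Amend Conducting the Research, item 2:

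1. Parents return their forms in a sealed envelope opened only by the research assistant who already scores EPDS and STAI-S, promptly enough that the score alerts are not delayed. Tell parents that the staff caring for their infant will not see their ratings, with the explicit exception that the existing follow-up of high EPDS or STAI-S scores or suicidal thoughts still applies. An unqualified promise would conflict with that follow-up.
2. Approach every eligible family consecutively from the daily discharge check, and log a reason for each one not approached if Appendix A does not already provide for it.
3. Use the same type of recruiter in both periods and record it for each family.

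The cost is envelopes, a sentence in the parent information, one log column and prompt opening of returns. The last needs some arrangement at weekends, because the Protocol budgets recruitment time for weekdays and treats weekends as preferable only.

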#### **3. Data entry to the REDcap**

- not included in this time allocation

## **Finances**

The units are responsible for the following costs related to the study. At least following costs need to be considered:

- Intervention costs (training fee + salary of the mentor nurses)
- Material (printing out the informed consent forms, information and instruction for the parents and staff, diaries)
- Desk computer/laptop and Internet access available for the study period for the web questionnaire
- Cost of the ethical approval
- Cost of research staff/ nursing staff participation
- Data entry

Data analysis is centralized and paid in Finland.

